### Sample size

On average, we will include cancer patients at 6 weeks or 42 days after diagnosis, and the follow-up time for the primary outcome return to work will be 12 months after inclusion, hence 12 months and 42 days after diagnosis. Earlier studies in our hospital showed that return to work for patients with various cancer types was 64 % at 12 months of follow-up from diagnosis [28]. In addition, earlier studies in our hospital showed that return to work in the first 42 days is around 8 % [28]. Therefore, the return to work for the control group was set at 64 % + 8 % = 72 %. In a study of Nieuwenhuijsen et al. [29], an intervention group of 35 radiotherapy patients received a supportive work-related intervention in a hospital. Time between diagnosis and the end of treatment was a median 42 days. Return to work was measured between the end of treatment and work resumption and was 89 % after 12 months. Therefore, the return to work for the intervention group in our intervention was also set at 89 %.

Based on our earlier studies on consecutive cancer patients, a power analysis indicated that we should include a total of 170 patients with a follow-up of 1 year after inclusion to indicate a difference of 89 % return to work in the intervention group versus a 72 % return-to-work rate in the control group, with a power of 80 % and *p* < 0.05. Accounting for 10 % loss to follow-up, 190 patients should be included.

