### Usual care in the Netherlands

Currently work-related issues are not structurally addressed as part of cancer (survivorship) care in the Netherlands. However, it is becoming more common to discuss this issue with a care provider at the hospital or to receive support by a reintegration office specialised in patients with cancer.

All sick-listed employees should have an occupational physician who should legally advise them about return to work according to the blueprint of evidence-based guidelines of the Dutch Association of Occupational Physicians [31]. The Improved Gatekeepers Act covers sick leave in the Netherlands and is in force during the first 2 years of sick leave. The act states that a sick-listed employee cannot be discharged and receives at least 70 % of his/her wage. The Improved Gatekeepers Act states that employers and sick-listed employees are together responsible for work resumption, which means that both parties can be sanctioned.

In the Netherlands, the social security system also provides a safety net for sick-listed workers without an employment contract according to the Improved Gatekeepers Act. Application of the Act is the same, except that these workers do not have an employer/workplace to return to. Sick-listed workers without an employment contract receive 70 % of their last daily wage during the first 2 years of sick leave. The Dutch Social Security Agency pays for the sick leave, is responsible for executing obligatory occupational health actions and should facilitate work resumption.

Self-employed persons can be privately insured against sickness absence, but most are uninsured because of the high costs. If a person is privately insured, it depends on the insurance policy as to when someone receives a supportive income, how much this supportive income is and whether or not he/she receives sickness absence counselling and vocational rehabilitation guidance.

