#### Economic evaluation

The economic evaluation will be conducted from a societal perspective. The following direct costs will be measured for both groups: costs to deliver the Cancer@Work intervention or costs to deliver care as usual and the following indirect costs: absenteeism, lost work productivity, lost earnings and work adjustments. The direct costs will be determined by means of the costs to deliver the Cancer@Work intervention (i.e. costs to develop and maintain the e-health intervention, average specialised nurse wage, the amount of time spent on each participant and training costs) or costs to deliver care as usual (i.e. average specialised nurse wage and the amount of time spent on addressing return to work of each participant). Absenteeism costs will be determined by means of total days on sick leave from the first day of sick leave until follow-up and on income and work productivity costs by the WLQ and on income [35, 36]. Additionally, lost earnings will be determined on the basis of the differences between income at baseline and income at follow-up. Work adjustments will be assessed by means of the cost of each work adjustment.

Direct costs will be acquired by the specialised nurses keeping track of the time spent on each participant and by the research team on keeping track of the costs to develop and maintain the Cancer@Work intervention and training costs to train specialised nurses to deliver the Cancer@Work intervention. Indirect costs will be acquired by a self-reported questionnaire completed by participants during follow-up.

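### Sick-leave days are priced on an income that the article never places before the start of sick leave, so work lost on reduced or no sick pay may be undervalued

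*Protocol article*

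**What the plan says.** Under Assessment of the outcomes, Economic evaluation, the protocol article sets the frame: "The economic evaluation will be conducted from a societal perspective". Three indirect-cost items then depend on income:

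- Absenteeism is based on "total days on sick leave from the first day of sick leave until follow-up and on income".
- Productivity loss is determined as "work productivity costs by the WLQ and on income".
- For the third item, "lost earnings will be determined on the basis of the differences between income at baseline and income at follow-up".

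On the source of the data: "Indirect costs will be acquired by a self-reported questionnaire completed by participants during follow-up". The section Prognostic and descriptive characteristics lists income only as an amount in euros per month. Under Statistical analysis, Economic evaluation, direct and indirect costs are summed for each participant, and the cost difference is divided by the difference in return-to-work rates.

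On timing, the Sample size section states: "On average, we will include cancer patients at 6 weeks or 42 days after diagnosis". The abstract requires patients to be on sick leave and places the baseline questionnaire before allocation.

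On sick pay, the section Usual care in the Netherlands gives employees a floor of 70% of wage. For others it says "Sick-listed workers without an employment contract receive 70 % of their last daily wage during the first 2 years of sick leave" and "Self-employed persons can be privately insured against sickness absence, but most are uninsured because of the high costs". The Participants section admits the self-employed.

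**The concern.** Absence is counted from the first day of sick leave, but every income the article mentions is collected weeks after that day. By the article's own account, income during sick leave can be well below the normal wage. If such an income prices the lost days, the cost of a lost day falls with the patient's sick pay. From a societal perspective the lost work is the same whether the patient is paid 100%, 70% or nothing.

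Income multiplies days in the absenteeism item, so a wrong income does not cancel between arms. It carries into the incremental cost and the cost-effectiveness ratio. The lost-earnings item has the same reference problem, but there it affects the reported level.

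**Working it through.** The article states no cost figure, so there is none to reproduce. The check applies the stated rules to an index wage.

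**Inputs**
- Normal wage before sick leave: W = 100 per month (index).
- Fraction received while sick: b = 1.0, 0.7 or 0. The first two span full pay and the 70% in Usual care in the Netherlands. The last assumes that an uninsured self-employed patient has no income.
- Months absent: 6 for a returner (assumed) and 13.4 for a non-returner. The latter is 12 months plus 42 days, 12 + 42/30, and assumes that sick leave began at diagnosis.
- Return to work: 89% versus 72% (Sample size), treated here as full return.
- Income is read as income received.

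**Absenteeism per patient, baseline income as multiplier:** months × b × W.
- b = 1.0: 600 (returner) and 1,340 (non-returner), which is the correct value.
- b = 0.7: 6 × 70 = 420 and 13.4 × 70 = 938. Both are 30% too low.
- b = 0: 0 and 0.

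**Absenteeism per patient, follow-up income as multiplier:** the returner is priced at W and the non-returner at b × W.
- b = 0.7: 600 and 938.
- b = 0: 600 and 0.

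The same absent day is now worth 100% of its value in a returner and 70% or 0% in a non-returner.

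**Arm difference in absenteeism, if every patient had the given b.** Mean months absent are 0.89 × 6 + 0.11 × 13.4 = 6.814 in the intervention arm and 0.72 × 6 + 0.28 × 13.4 = 8.072 in the control arm, a difference of −1.258.
- Priced at W: −1.258 × 100 = −125.8.
- Baseline income, b = 0.7: −1.258 × 70 = −88.1. With b = 0: 0.
- Follow-up income, b = 0.7: 0.17 × (600 − 938) = −57.5. With b = 0: 0.17 × (600 − 0) = +102, so the sign reverses.

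**Lost earnings per month:** baseline income minus follow-up income.
- b = 0.7: 70 − 70 = 0 while still off work, and 70 − 100 = −30 after full return. Measured from W they would be 30 and 0.
- b = 0: 0 while off work and −100 after return. Measured from W they would be 100 and 0.

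**Arm difference in lost earnings.** With b = 0.7, mean follow-up income is 0.89 × 100 + 0.11 × 70 = 96.7 versus 0.72 × 100 + 0.28 × 70 = 91.6. The arm difference in lost earnings is −5.1 whether the reference is 70 or 100. With b = 0 it is −17 either way. The baseline term is the same on average in randomised arms and drops out.

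**WLQ productivity costs.** The same multiplier problem applies if baseline income is used. If follow-up income is used, patients back on full pay are priced normally.

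**The case against.** The strongest reply is that when a question is asked does not fix which income it asks about. A questionnaire completed during sick leave can ask for contract salary or usual business income, and questionnaire wording is detail that an article may leave to the full protocol. If it asks for that income, the undervaluation disappears. This stands, and it makes the conclusion conditional. It does not dispose of the point, because the article does state a rule. A difference between baseline and follow-up income, with no normal or contract wage named, reads most naturally as income received at those times.

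Second, the lost-earnings rule, where the wording is most explicit, does not bias the planned comparison. This also stands. A reader might infer from the negative values that the arm difference in lost earnings is wrong, but the arithmetic shows that it is not, on average.

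Third, the Participants section does not repeat the sick-leave criterion, and the Sample size section puts return to work in the first 42 days at around 8%. Some entrants may therefore already be back at work. That leaves most still absent at baseline and does not change the argument.

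Fourth, simply substituting income from before sick leave everywhere would charge the same lost work twice, because the indirect costs are summed. This is correct, and the fix allows for it.

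**Conclusion.** The point holds conditionally. If income received is what is recorded, absence is undervalued by 30% for patients on 70% pay, and entirely for an uninsured self-employed patient with no income. Baseline income as the multiplier shrinks the absenteeism difference between arms. Follow-up income also makes the price of a day depend on the outcome. The level of lost earnings is distorted and can be negative, but its arm difference is not affected on average. Patients on full sick pay are unaffected.

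Three stronger readings are not supported:

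- A reader might infer that undervaluation falls only on patients still on sick pay at follow-up. That fits follow-up income as the multiplier. With baseline income, patients who later return are undervalued too, and the article does not say which is used.
- A reader might put a percentage on the whole trial. Suppose a share s is self-employed, 80% of them without income and the rest at 70%, with employees at a fraction e of wage. The valued fraction is (1 − s) × e + s × 0.2 × 0.7. It runs from 0.957 (s = 0.05, e = 1) to 0.588 (s = 0.20, e = 0.7), an understatement of 4% to 41%. None of these shares is in the documents, and the upper end needs every employee on the legal minimum. This is a scenario range, not an estimate.
- A reader might take uninsured to mean no income. The article says only that most self-employed people are uninsured.

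The issue is confined to the economic evaluation. The primary outcome and the clinical secondary outcomes are untouched. It should still be corrected, because it can change the cost-effectiveness ratio and the correction is cheap.

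**What to change.** Ask each participant once for usual monthly earnings before the first day of sick leave, using a follow-up questionnaire for those already enrolled. State in the Economic evaluation section that this figure is the fixed multiplier for absenteeism and for WLQ productivity costs, in both arms and at all time points. If lost earnings are reported, measure them from the same figure, but show them separately and do not add them to absenteeism in the societal total for the same period. Otherwise a patient without income who earned 100 per month would be charged 100 for the absence and 100 again for the earnings.

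The cost is one extra question, a short wording change and some recall error, which may be larger for self-employed people with variable income. If the questionnaire already asks for contract or usual earnings before sick leave, a clarifying phrase settles which income is used, and only the separate reporting of lost earnings remains to be added.

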#### Intermediate effect of the Cancer@Work intervention on self-management and work-related self-efficacy

The Cancer@Work intervention is a self-management intervention based on problem-solving techniques and cognitive behavioural techniques. The key mechanisms of the Cancer@Work intervention are therefore self-management skills and work-related self-efficacy. To measure this change in self-management skills, we will measure perceived confidence in own self-management skills on a visual analogue scale of 0 (no confidence) to 100 (high confidence). Work-related self-efficacy will be measured with the 11-item questionnaire ‘expectations regarding work functioning’ [43] with higher scores indicating more self-efficacy regarding work.

### Statistical analysis

All analyses will be based on the intention-to-treat (ITT) principle. All baseline data and data regarding primary and secondary outcomes as well as data from the feasibility evaluation will be presented using descriptive statistics. Differences in baseline data between the intervention and control group will be assessed using Student’s *t* test for continuous data and the chi-squared test for categorical data.

#### Feasibility evaluation

The following feasibility outcomes will be described according to the Bowen scheme [33]: acceptability, demand, practicality and compliance with the Cancer@Work intervention. The following baseline parameters will be analysed to verify whether they are related to non-compliance: treatment type, treatment duration, age, education, gender, need for cognition regarding return to work, need for support with return to work, existence of problems with work, expectations concerning return to work, expectations concerning the Cancer@Work intervention, Internet skills and self-management skills. The following parameters measured at follow-up on patient level by means of self-reported questionnaires will be related to non-compliance: whether or not their expectations about the Cancer@Work intervention are fulfilled, work situation at follow-up and satisfaction with the Cancer@Work intervention.

#### Effectiveness

The relative risk and 95 % confidence interval for returning to work at 12 months of follow-up will be calculated for the intervention group versus the control group. In addition to this ITT analysis aimed at ’all-cause return to work’, the analysis will be performed excluding those patients who have died during follow-up and those who have a life expectancy of less than a few months, because they will not return to work.

To assess whether the Cancer@Work intervention is more effective for those who need it most, a planned subgroup analysis for patients with a high risk of not returning to work will be performed. This subgroup will be identified based on having physical heavy work, low work ability at baseline, high levels of fatigue, depression and cognitive problems at work at 3 and 6 months of follow-up and a long duration of cancer treatment [13, 30]. In addition, to ascertain whether the Cancer@Work intervention is more effective for various subgroups of patients who are more or less prone to benefit from self-management, a subgroup analysis will be done for young versus old, male versus female and lower education level versus higher education level [44].

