**Methods:**

We designed a multi-centre randomised controlled trial with a follow-up of 12 months. Patients who have paid employment at the time of diagnosis, are on sick leave and are between 18–62 years old will be eligible to participate. After patients have signed the informed consent form and filled in the baseline questionnaire, they are randomly allocated to either the nurse-led, stepped-care, e-health intervention called Cancer@Work, or care as usual. The primary outcome is sustainable return to work. Secondary outcomes are sick leave days, work ability, work functioning, quality of life, quality of working life and time from initial sick leave to full return to work without extensive need for recovery. The feasibility of the Cancer@Work intervention and direct and indirect costs will be determined. Outcomes will be assessed by questionnaires at 3, 6, 9 and 12 months of follow-up.

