Previous studies on cancer and work have taught us three main things. First, self-assessed work ability is an important prognostic factor for return to work, irrespective of clinical characteristics [7, 13]. This finding has led to the hypothesis that return to work is influenced by patients’ expectations and beliefs regarding return to work and that addressing misconception or improving someone’s self-efficacy would enhance return to work [13]. A successful approach to increase someone’s self-efficacy is the involvement of self-management interventions [14] which might be based on cognitive behavioural techniques [15] or problem-solving techniques [15, 16]. Second, both employers and colleagues as well as cancer care providers are important stakeholders in the return to work of patients with cancer [11]. It has appeared difficult to connect with the workplace from the hospital [17], but a successful approach to solve this problem might be the use of integrative-care management [18]. Third, the longer the duration of sick leave, the more difficult it is to return to work [19]. Addressing return to work in an early phase during cancer treatment might therefore be the window of opportunity. Moreover, two studies showed that cancer patients appreciated receiving information on their return to work during early cancer treatment [8, 17]. For these reasons, we choose to develop an early intervention based on the theory of self-management and integrative-care management.

Numerous studies have demonstrated that e-health is a suitable way of delivering self-management interventions for various conditions, including cancer [20, 21], and to deal with various problems, including return to work [22, 23]. In addition, e-health proved suitable for delivering an integrative-care management intervention as well [24]. Based on these findings, we choose to deliver the intervention as an e-health intervention. We define e-health as the process of providing the intervention partly over the Internet including interaction with health care providers.

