### Assessment of the outcomes

Data will be both self-reported and collected by recording use of the Cancer@Work intervention by participants and recording the content of the assignments made by participants. The self-reported outcomes will be assessed at baseline and at 3, 6, 9 and 12 months of follow-up using questionnaires that will be completed by participants randomised to the intervention group and control group with online software. All participants will receive an email with a link to complete the questionnaire online if they indicate to prefer questionnaires online; otherwise, they will receive paper questionnaires. Completing a questionnaire will take approximately 30 minutes.

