#### Effect evaluation

The primary outcome of sustainable return to work is measured as any return to work (yes/no) at follow-up independent to the number of contract hours which is sustained for at least 4 consecutive weeks without recurrent sick leave. Return to work is either partial return to work (working a part of contract hours) or full return to work (working all contract hours).

The secondary outcomes are full return to work (yes/no) at follow-up defined as working the hours stated in the work contract, time to any (either partial or full) return to work in days from the first day of sick leave to the date of any return to work and time to return to work in days from the first day of sick leave to the date of full return to work. These return-to-work measures must be sustained for at least 4 consecutive weeks. Furthermore, secondary outcome measures are work ability using the first three questions of the Work Ability Index (WAI) [34], work functioning using the Work Limitations Questionnaire (WLQ) [35, 36], quality of life using the SF-12 [37], quality of work life using the QWLQ-CS (De Jong et al. in preparation) [38] and the time from initial sick leave to full return to work without extensive need for recovery using a subscale of the ‘perception and assessment of work questionnaire’ (VBBA) [39].

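### The primary relative risk uses no covariate although baseline work ability, which the protocol calls prognostic, is collected: a valid analysis that gives up some precision

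*Protocol article*

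**What the plan says.** The Effect evaluation section makes the primary outcome binary: "The primary outcome of sustainable return to work is measured as any return to work (yes/no) at follow-up". The Effectiveness section then gives the estimator: "The relative risk and 95 % confidence interval for returning to work at 12 months of follow-up will be calculated for the intervention group versus the" usual-care arm. It names no covariate, stratification term or model.

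Four other places bear on this:

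- The Background says that "self-assessed work ability is an important prognostic factor for return to work, irrespective of clinical characteristics".
- Work ability is a secondary outcome, scored from the first three Work Ability Index (WAI) questions (Effect evaluation). On timing, "The self-reported outcomes will be assessed at baseline and at 3, 6, 9 and 12 months of follow-up" (Assessment of the outcomes).
- The abstract puts that baseline measurement ahead of allocation: "After patients have signed the informed consent form and filled in the baseline questionnaire, they are randomly allocated".
- In the effectiveness analysis, baseline work ability appears only in the definition of a high-risk subgroup ("low work ability at baseline").

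Randomisation is stratified by hospital department and by age at 50 years, not by work ability. The only covariate adjustment in the article is a Cox model for the secondary time-to-event outcomes. It applies only if baseline tests show significant differences between the arms.

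**The concern.** A baseline variable that predicts the outcome can sharpen a randomised comparison. It explains part of the variation between patients and removes the effect of any chance difference between the arms on that variable. Here the protocol itself names such a variable, collects it before allocation and does not stratify on it, yet leaves it out of the primary comparison.

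The stake is the width of one confidence interval. The trial is sized at 80 % power for a 17-point difference, so it has little reserve if the true effect is smaller. The article also gives no rule for the primary result if the arms happen to differ on work ability. An adjustment chosen after seeing the data would be less credible than one fixed beforehand.

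**Working it through.** **Inputs from the Sample size section.** Control 72 %, intervention 89 %, 80 % power, p < 0.05, 170 patients before dropout. Sidedness is not stated; two-sided reproduces the stated number. Equal arms (85 each) are assumed from the stated aim of equal group sizes.

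**1. The plan's own figure.** For the pooled two-proportion test the mean risk is 0.805.

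n per arm = [1.960·√(2·0.805·0.195) + 0.842·√(0.72·0.28 + 0.89·0.11)]² / 0.17²
= [1.960·0.5603 + 0.842·0.5473]² / 0.0289 ≈ 84.1, so 85 per arm and 170 in total.

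This matches exactly. Power at 85 per arm is Φ[(0.17·√85 − 1.098)/0.5473] = Φ(0.857) = 80.4 %. The planned power is that of a crude comparison, and the crude analysis delivers it.

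On the log relative risk scale, ln(0.89/0.72) = 0.212 and SE = √(0.28/(0.72·85) + 0.11/(0.89·85)) = 0.0776. The normal approximation then gives Φ(0.212/0.0776 − 1.96) = 77.9 %. Simulated power of the crude relative risk test was 80 to 82 %.

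**2. What adjustment adds.** The documents give no association between baseline work ability and return to work, so a range was assumed. Each scenario had 6,000 simulated trials with 85 per arm, a normal covariate, a logistic outcome and marginal risks fixed at 0.72 and 0.89. The adjusted estimate averages the fitted risks over all patients, first as if all were in the intervention arm and then as if all were in the control arm. It takes the ratio of the two averages, with an influence-function standard error. Efficiency is the crude variance divided by the adjusted variance.

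| Assumed odds ratio per SD | Crude power | Adjusted power | Gain (points) | Efficiency |
|---|---|---|---|---|
| 1.0 | 81.4 % | 81.2 % | −0.2 | 1.00 |
| 1.5 | 80.6 % | 81.5 % | 0.9 | 1.02 |
| 2.0 | 80.2 % | 83.1 % | 2.9 | 1.05 |
| 2.5 | 82.3 % | 85.7 % | 3.4 | 1.10 |
| 3.0 | 80.7 % | 85.8 % | 5.1 | 1.14 |
| 4.0 | 81.0 % | 88.9 % | 7.9 | 1.24 |

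Separate runs gave gains of about 5 points at 2.7 and 7 to 8 at 3.7. Crude power does not depend on the odds ratio, because the marginal risks are fixed; its spread down the column is simulation error (√(0.8·0.2/6000) ≈ 0.5 points). Both methods compare the same simulated trials, and their mean log relative risks agree to within 0.001, so the estimand is unchanged. Type I error of the adjusted test was 4.1 to 4.8 %.

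**3. In patients.** Effective size is 170 × efficiency: about 173 at odds ratio 1.5 (170·1.02), 179 at 2.0 (170·1.05) and 194 at 3.0 (170·1.14).

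**4. Chance imbalance.** The difference in arm means of an unstratified covariate has standard error √(2/85) = 0.153 SD. The arms therefore differ by at least 0.2 SD in about 19 % of trials. Near the 72 % control risk, the shift in risk is about 0.2·ln(OR)·0.72·0.28·(1 − R²). With the simulation's control-arm R², this gives 0.2·0.693·0.2016·(1 − 0.084) = 2.6 points at odds ratio 2 and 0.2·1.099·0.2016·(1 − 0.177) = 3.6 points at 3, against a planned 17. This is the same noise as in step 2, seen in a single trial; it is not an additional loss.

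**The case against.** **The text never calls the analysis unadjusted, and a journal article may leave covariates to the analysis plan.** This is partly right: the crude reading is drawn from a bare two-group relative risk. But the article does not simply defer the matter. It states the primary estimator, then states an adjustment rule and attaches that rule only to secondary time-to-event outcomes. If an analysis plan already adjusts the primary comparison, the article's sentence only needs aligning with it.

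**The crude analysis is valid and meets its target.** This stands in full. A reader might infer that the primary result would be biased, or the trial underpowered on its own assumptions. The documents support neither: randomisation protects the crude relative risk, chance imbalance is already reflected in its confidence interval, and 85 per arm gives 80.4 %.

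**The size rests on an assumed association.** This also stands. A reader might take the Background's wording to imply a correlation near 0.5. The variance would then fall by 25 %, and 170 patients would act like 170/0.75 = 227, or 57 more. Odds ratios as high as 5 per SD would bring power to about 91 %. Nothing in the documents supports an association that strong. Patients are enrolled on sick leave a few weeks after first treatment, and the outcome is any return, even partial, by 12 months; both could weaken the link. Scaling the variance by one minus the squared control-arm correlation also slightly overstates the gain: at odds ratio 2.7 it gives an efficiency of 1.16, against 1.13 simulated.

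**Department and age may carry some of the same information.** A reader might infer from the Background that they carry none of it. That is not shown. The simulations compare one covariate with a crude analysis, so the increment over an analysis adjusted for the stratification factors is unknown and may be smaller.

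**Conclusion.** The point holds as a recommendation on efficiency. The stated primary analysis sets aside a pre-randomisation measurement that the protocol itself calls prognostic, and so gives up precision it could have from the same patients. The plan is not wrong and the crude result would not be invalid.

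The gain is about 1 point of power at an odds ratio of 1.5 per SD, 3 at 2.0, 5 at 2.7 and 7 to 8 at 3.7. If work ability does not predict at all, essentially nothing is lost (81.4 % against 81.2 %). These figures assume 85 analysed patients per arm, the planned risks, a single approximately normal score with the same odds ratio in both arms, complete baseline data, and a comparison with a fully crude analysis. The documents do not show where in the range the truth lies.

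**What to change.** In the Effectiveness section, pre-specify the following before outcomes are compared by arm:

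- The primary relative risk at 12 months is adjusted for baseline work ability, entered as the continuous score of the three WAI items.
- A logistic model with arm and baseline work ability is fitted and standardised to the marginal risk in each arm. The ratio of these risks is reported with a robust or bootstrap 95 % confidence interval.
- The adjustment is always made. It is not triggered by baseline significance tests, unlike the Cox rule for the secondary outcomes.
- A missing baseline score is filled with a simple value, such as the mean over both arms, so that no randomised patient is dropped for it.
- The crude relative risk is reported as a supporting analysis.

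This costs a few lines of text and modest programming, with no new patients, visits or questionnaires. The one real downside is that the headline estimate becomes model-based and less transparent than a two-by-two table; reporting the crude relative risk beside it largely answers that.
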